### Blinding

Due to the specific nature of acupuncture, it is not feasible to blind practitioners. Therefore, blinding will be implemented for the participants, evaluators, and statisticians. Practitioners adhere to strict confidentiality protocols to avoid disclosing group allocation to the participants and evaluators. Evaluators are responsible for collecting and analyzing the data unrelated to the treatment process and are not exposed to any information about group allocation throughout the study. Statisticians are solely responsible for data analysis and are not involved in the treatment process, thereby ensuring the objectivity and impartiality of the results.

To evaluate participant blinding integrity, Bang’s Blinding Index (BI) will be calculated at the completion of the treatment phase (17). After the final treatment session, the participants will be asked to guess their group allocation (real acupuncture, sham acupuncture, or unsure) and to rate their confidence in this guess.

The Credibility/Expectancy Questionnaire (CEQ) (18) will be administered after the first treatment session. Group differences in the CEQ scores will be examined to verify that expectancy was balanced between the groups.

After the completion of statistical analysis, the unblinding procedure will be initiated. Researchers responsible for unblinding will disclose group information to the data analysts as necessary to finalize comparisons and interpret the study results.

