### Safety monitoring and adverse event reporting

To maximize participant safety and proactively minimize risks, all participants will undergo a careful anamnesis and baseline assessment before the first treatment. During the study, the participants undergoing acupuncture treatment may experience adverse events (AEs), including but not limited to pain, subcutaneous congestion, hematoma, local infection, and, in rare cases, severe events such as syncope. Safety assessments will encompass vital sign measurements (blood pressure, heart rate, respiration rate, body temperature) and physical examinations. These vital sign measurements will be performed before the start of the protocol (at baseline assessment) and at key points during the treatment period (before and after treatment). Their primary purpose will be to monitor participant safety and ensure early detection of potential adverse reactions, rather than to serve as clinical indicators of acupuncture efficacy. Detailed documentation of AEs will include the time of occurrence, duration, classification, severity, remedial actions, and final resolution. Participants will be instructed to report any abnormal reactions or discomfort, which will be carefully documented, including the time, severity, and potential causes. Regardless of their relationship to the treatment, all AEs will be promptly and appropriately managed, recorded in the Case Report Forms (CRFs), and reported to the study director and the Ethics Committee of the Affiliated Hospital of Shandong University of Traditional Chinese Medicine.

Mild and moderate AEs will be managed symptomatically and monitored, while severe AEs, such as death, life-threatening disability, or hospitalization, will receive emergency treatment and will be reported to the Research Ethics Committee within 24 h, which will provide guidance on whether the trial should be terminated. To minimize the risk of severe adverse events, all practitioners have received specific training on recognizing and managing autonomic adverse responses to acupuncture, consistent with safety guidelines outlined in recent systematic reviews (29, 30).

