Bang’s Blinding Index will be calculated for each group with 95% confidence intervals using the Wilson score method. Blinding will be considered successful if BI values are close to zero (|BI| < 0.3). Group differences in the CEQ scores will be compared using independent samples *t*-tests (or the Mann–Whitney U test if data are non-normally distributed). If the CEQ scores differ significantly between the groups, sensitivity analyses will include the CEQ as a covariate in primary outcome models (ANCOVA or mixed models) to adjust for potential expectancy effects. Correlation analyses will explore associations between the CEQ scores, acupuncture sensation scores, and primary outcomes to identify potential mediators of treatment effects.

Safety analysis will include the incidence of adverse events (AEs) during the study, with group comparisons of treatment-related adverse events conducted using a chi-squared test or Fisher’s exact test. Additional analyses may be conducted as deemed appropriate, with further details provided in the statistical analysis plan. Statistical significance will be set at a *p*-value of <0.05 for all analyses.

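### The only adverse-event comparison with a named between-group test is of treatment-related events; an any-cause comparison should be named beside it

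*Protocol article*

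**What the plan says.** Four statements in the protocol article bear on this.

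- Data analysis, on overall incidence: "Safety analysis will include the incidence of adverse events (AEs) during the study".
- The same sentence then gives the between-group test: "with group comparisons of treatment-related adverse events conducted using a chi-squared test", with Fisher's exact test as the alternative. The next sentence leaves the rest open: "Additional analyses may be conducted as deemed appropriate, with further details provided in the statistical analysis plan".
- Safety monitoring and adverse event reporting: "Regardless of their relationship to the treatment, all AEs will be promptly and appropriately managed, recorded in the Case Report Forms (CRFs". The section also has potential causes written down for reported reactions. It does not say who decides relatedness, on what scale, or whether that person is blinded.
- Blinding: "it is not feasible to blind practitioners", whereas "blinding will be implemented for the participants, evaluators, and statisticians".

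Data management adds that the investigator completes the case report form, without saying whether that investigator is blinded. The safety set is everyone who received at least one treatment.

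**The concern.** An AE of any cause either happened or did not. Whether it was related to treatment is an opinion formed after randomisation, and someone who knows the group may form it differently in the two arms. The arms are plain to the practitioner: needling to between 0.5 and 1.2 cun with deqi in one, about 2 mm without manipulation in the other. If attribution differs by arm, a test on related events mixes the effect of treatment on AEs with the effect of group on labelling. It can then show a difference where none exists or mask one that does.

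The comparison without the attribution step can be made from data the trial already collects, yet no between-group test is expressly assigned to it. Both the Introduction and the Discussion present acupuncture as having few adverse effects, so the safety contrast is likely to be quoted in support of that message.

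**Working it through.** **No figure to reproduce.** The article gives no AE rate, no attribution rate and no power statement for safety. The only design inputs are the group sizes, 120 and 60 (Randomization and allocation concealment; Sample size), and the 0.05 significance level (Data analysis). Every rate below is an assumption, chosen to show direction and possible scale.

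**Method.** Let p be the true proportion with an AE in a group and r the proportion of those who are called related. The tested proportion is p × r. The rejection probability is the sum, over all pairs of counts in 120 and 60, of the two binomial probabilities for pairs where the two-sided test gives p < 0.05. The chi-squared test is uncorrected.

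**Case A: no true difference, 20% in each group.**

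| Attribution, acupuncture / sham | Tested proportions | Chi-squared | Fisher |
|---|---|---|---|
| All AEs, no attribution step | 20% / 20% | 0.051 | 0.039 |
| 80% / 50% | 0.20×0.80 = 16%; 0.20×0.50 = 10% | 0.185 | 0.146 |
| 90% / 50% | 18% / 10% (ratio 1.80) | 0.285 | 0.242 |
| 90% / 40% | 18% / 8% | 0.448 | 0.388 |
| 50% / 90% | 10% / 18% (ratio 0.56) | 0.342 | 0.286 |

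Equal attribution does no harm here: at 70% in both arms Fisher's test rejects with probability 0.036. The trouble comes only from unequal attribution.

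**Case B: a true difference, 30% against 15%.**

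| Attribution, acupuncture / sham | Tested proportions | Chi-squared | Fisher |
|---|---|---|---|
| All AEs, no attribution step | 30% / 15% (ratio 2.0) | 0.615 | 0.582 |
| 60% / 90% | 0.30×0.60 = 18%; 0.15×0.90 = 13.5% | 0.110 | 0.091 |
| 50% / 100% | 15% / 15% | 0.050 | 0.036 |
| 90% / 50% | 27% / 7.5% (ratio 3.6) | 0.918 | 0.903 |

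So the same mechanism can create, hide or exaggerate a difference.

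**Case C: where the related-event test is the better one.** Assume accurately labelled needle-related AEs in 20% against 5%, plus an independent background AE rate of 20% in each arm. Any-cause proportions are 1 − 0.80×0.80 = 36% and 1 − 0.95×0.80 = 24%. Chi-squared power is 0.84 on related events and 0.37 on all events. Background events dilute a real needle effect, so replacing the planned comparison would lose something.

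**The case against.** **All-AE incidence is planned.** This stands. A reader might infer that only treatment-related events will be analysed; the first half of the same sentence rules that out. With counts by arm, anyone could form the any-cause contrast. The Data analysis section also has a sentence on testing categorical data between groups by chi-squared or Fisher, which could be read as a general rule. It sits with the description of baseline characteristics, so that reading is possible but not secure.

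**The SAP may supply the comparison.** It may; it is not at hand, and the choice of AE tables is ordinary SAP content. What remains is a choice the article does state: it assigns the named test to the attributed subset. The clause about additional analyses is permissive and commits to nothing for all AEs.

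**No one is said to judge relatedness unblinded.** This also stands. A reader might infer that the practitioners assign the label. The article does not say so, evaluators are blinded, and the Discussion separates treatment, assessment and analysis between researchers. The supportable statement is that no blinded assessor of relatedness is named.

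**The calculated error rates prove nothing about this trial.** Correct. The attribution splits are invented. They count as false positives only if the labelling difference is error; deeper needling could truly cause more related events. The listed events, such as hematoma or pain, are also mostly local to the needle, which may leave less room for misattribution.

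**The any-cause comparison is no gold standard.** Agreed. Unblinded practitioners could influence which events are elicited and recorded, and Case C shows the dilution. It removes the attribution step and nothing more. These points argue for putting the two comparisons side by side, not for substituting one for the other.

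**Conclusion.** The point holds as a limited one. The article plans to report overall AE incidence, but the only AE contrast to which it expressly attaches a between-group test is of treatment-related events. That label is a post-randomisation judgement, in a trial with unblinded practitioners and no named blinded assessor of relatedness, so the contrast could be biased either way.

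The size is unknown. Under the assumed rates the probability of a spurious chi-squared result runs from about 18% to 45%, and power against a true 30% versus 15% difference falls from 62% to between 5% and 11%. These figures show what unequal attribution could do; they do not estimate what it will do. The documents do not support a claim that the safety comparison is biased, or that any-cause AEs should displace the treatment-related comparison.

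This is a minor improvement to the safety analysis. AEs are listed as neither a primary nor a secondary outcome, and the efficacy analysis is unaffected.

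**What to change.** In the Data analysis section, add that the proportion of participants with at least one AE of any cause will also be compared between groups in the safety set, with the risk difference and its 95% CI alongside the chi-squared or Fisher test. Present it beside the treatment-related comparison, which is kept. Report the needle events listed under Safety monitoring by group with confidence intervals, descriptively; separate significance tests for each would add multiplicity for little gain.

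The cost is a sentence and one extra table. All AEs are already recorded, so no new data, participants or procedures are needed. The downside is that background events dilute the any-cause contrast, so a null result there should not be read as the absence of a needle effect. Recruitment is still open by the article's account and no interim efficacy analysis is planned, so the change can be fixed before unblinding.

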### Quality control

The acupuncture procedure will primarily be carried out by acupuncture specialists with more than 10 years of clinical experience. A launch meeting has been convened before the formal initiation of the trial to provide training on the purpose and design of the trial, treatment strategies, and quality control for all staff. The clinical participants will be required to complete the CRFs according to the design requirements, filling them in carefully and in detail. The study medical records and the CRFs shall be the original records and shall not be altered. All data in the clinical trial should be recorded, and the original report (or copy) should be attached to the case report form. Data that are significantly high or outside the clinically acceptable range will be verified, and necessary explanations will be provided by the physicians participating in the clinical trial. Clinical supervisors make regular on-site visits to research centers, check original information on a sample basis, hold regular meetings on specific issues, and provide timely feedback in the form of supervision reports and subject briefings to improve the quality of supervision.

### Patient and public involvement

Patients and the public are not involved in the planning, design, recruitment, or conduct of the study. The results of the study will be disseminated to the participants and the broader public through various channels, including educational talks, booklets, and publication in open-access peer-reviewed journals.

### Ethics and dissemination

This study was approved by the Ethics Committee of Shandong University of Traditional Chinese Medicine on 6 March 2024 (2024–014-01-KY) and conforms to the principles of the Declaration of Helsinki. The trial is registered in the Chinese Clinical Trial Registry (Registration No: ChiCTR2400084720; Register date: May 23, 2024). Written informed consent will be obtained from all participants prior to their inclusion in the trial. Data will be handled anonymously, and only participant codes will be available in the central database to protect confidentiality. All personal information outside the scope of this trial will not be collected, shared, or maintained. Participants retain the right to withdraw from the study at any time. The results of this study will be disseminated through publications in peer-reviewed journals and presentations at academic conferences.

### Trial status

Recruitment for this study began on 23 May 2024 and is scheduled to continue until 31 December 2026. The trial is currently in the participant recruitment phase.

## Discussion

First, given the inherent nature of acupuncture interventions, blinding of the treating practitioner is unfeasible, which may introduce bias. However, throughout the trial, different researchers will oversee random allocation, patient recruitment, acupuncture treatment, outcome assessment, and data analysis to mitigate bias.

Second, this trial does not include an active pharmacologic control group, such as topiramate, propranolol, or CGRP monoclonal antibodies, which represents a significant limitation. While this trial is designed to assess whether acupuncture is superior to sham acupuncture in reducing monthly headache days, the magnitude of its benefit relative to established guideline-recommended drug treatments will remain uncertain. This will limit our ability to definitively position acupuncture within the treatment algorithm for chronic migraine prevention.

However, this limitation should be interpreted in context. The primary objective of this exploratory trial is to establish whether acupuncture produces specific effects beyond placebo—a necessary first step before investing in large-scale comparative effectiveness trials. Prior network meta-analyses have suggested that acupuncture demonstrates efficacy comparable to topiramate and other first-line preventives for chronic migraine (31), and recent head-to-head trials have shown non-inferior efficacy with superior tolerability (32). Nonetheless, future multi-arm trials directly comparing acupuncture, sham acupuncture, and active drug controls are warranted to provide definitive evidence for clinical guideline development, insurance coverage decisions, and shared decision-making between patients and clinicians regarding optimal treatment selection.

Third, the study employs a relatively short 8-week post-treatment follow-up period, which limits the assessment of long-term efficacy and durability. Migraine prevention guidelines often recommend 3–6 month follow-up to comprehensively assess sustained effects and potential relapse rates, which our 8-week window cannot capture. While this timeframe is shorter than in some prominent acupuncture and pharmacologic trials, it represents a scientifically sound and pragmatically feasible design for an exploratory study focused on short-term prophylactic efficacy. Therefore, should this trial demonstrate efficacy, future confirmatory studies with extended follow-up (e.g., 6–12 months) will be essential to fully characterize acupuncture’s long-term potential, identify relapse patterns, and establish evidence-based maintenance recommendations.

Chronic migraine (CM) is a neurovascular disorder that imposes a significant burden on individuals and healthcare systems globally (15, 33). Despite the availability of pharmacological treatments, including nonsteroidal anti-inflammatory drugs (NSAIDs), opioids, and triptans (4), these interventions present several limitations (34). Many patients report inadequate pain relief, frequent recurrence, and adverse effects, such as gastrointestinal disturbances and medication overuse headaches (9), which undermine long-term compliance and efficacy (35).

As a non-pharmacological intervention, acupuncture is associated with fewer side effects and has shown potential in reducing headache frequency, intensity, and duration (36–38). Moreover, it may alleviate associated symptoms and enhance overall wellbeing (32).

This study aims to provide recent high-quality evidence on the clinical efficacy of acupuncture for chronic migraine (CM). This randomized controlled trial will offer detailed and clinically relevant insights into the mechanisms and effects of acupuncture in CM management.
